## Abstract

**Background:**

An estimated 366 million people are living with diabetes worldwide and it is predicted that its prevalence will increase to 552 million by 2030. Management of this disease and its complications is a challenge for many countries. Optimal glycaemic control is necessary to minimize complications, but less than 70% of diabetic patients achieve target levels of blood glucose, partly due to poor access to qualified health care providers. Telemedicine has the potential to improve access to health care, especially for rural and remote residents. Video teleconsultation, a real-time (or synchronous) mode of telemedicine, is gaining more popularity around the world through recent improvements in digital telecommunications. If video consultation is to be offered as an alternative to face-to-face consultation in diabetes assessment and management, then it is important to demonstrate that this can be achieved without loss of clinical fidelity. This paper describes the protocol of a randomised controlled trail for assessing the reliability of remote video consultation for people with diabetes.

**Methods/Design:**

A total of 160 people with diabetes will be randomised into either a Telemedicine or a Reference group. Participants in the Reference group will receive two sequential face-to-face consultations whereas in the Telemedicine group one consultation will be conducted face-to-face and the other via videoconference. The primary outcome measure will be a change in the patient’s medication. Secondary outcome measures will be findings in physical examination, detecting complications, and patient satisfaction. A difference of less than 20% in the aggregated level of agreement between the two study groups will be used to identify if videoconference is non-inferior to traditional mode of clinical care (face-to-face).

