### Aims and objectives

In this study we are seeking to identify if telemedicine is a reliable vehicle for providing specialty consultation for people with diabetes using videoconferencing, with the implication that it would be useful to utilise when usual care is either not available or difficult to deliver. The aim of the study is to test the level of clinical agreement achieved using specialist to patient videoconferencing (VC) compared with face-to-face (FTF) consultation. To place this level of agreement in context, it will also establish the level of agreement among specialists using face-to-face consultation. This approach enables the variation in clinical decision making among clinicians to be identified, and thus to be differentiated from the effect of the VC mode of service delivery.

This study will test the hypothesis that the clinical assessment and recommendations as determined by an alteration in medication type or dose made by endocrinologists for people with diabetes via videoconference are significantly different from those made through face-to-face consultation (null hypothesis). Secondary hypotheses will apply the same analytic techniques to the other aspects of diabetes consultation: (i) ordering lab tests or other diagnostic intervention; (ii) initiation of new medication(s) or dose adjustment of the previously prescribed drugs for dyslipidaemia and/or hypertension; (iii) detection or management of diabetes related complications; and (iv) referring to other specialists or arranging hospital admission.

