### Sample size

This study will evaluate if agreement on the recommendations for the Telemedicine group is not inferior to agreement in the Reference group by more than an acceptable amount. This clinically acceptable amount of variation for diabetes consultation was set as 20% by a group of expert specialist consultants who had more than five years of telemedicine experience. The sample size is calculated based on the incidence rates of 25, 50, 25% for major change, minor change, and no change respectively in the patient medication made by the endocrinologists (significance level 5%, power 80%). It will be possible with a total of 160 participants (80 per each group) to detect any statistically significant difference for the true kappa of 0.7 and the null kappa of 0.5.

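### The stated non-inferiority rule compares the difference in agreement with 20% without a confidence bound, and the stated null carries no margin; read literally, a true loss equal to the margin passes in about 46–47% of trials

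*Protocol article*

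**What the plan says.** Three places in the protocol article bear on how the primary conclusion is reached.

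- **Abstract, Methods/Design.** "A difference of less than 20% in the aggregated level of agreement between the two study groups will be used to identify" whether video is non-inferior to face-to-face care. No interval, test or direction accompanies this.
- **Aims and objectives.** The hypothesis is that recommendations made by video "are significantly different from those made through face-to-face consultation (null hypothesis". No margin and no direction are given.
- **Sample size.** The aim is to see whether "agreement on the recommendations for the Telemedicine group is not inferior to agreement in the Reference group by more than an acceptable amount". On the margin: "This clinically acceptable amount of variation for diabetes consultation was set as 20% by a group of expert specialist consultants". The 160 participants are then justified at a 5% significance level and 80% power as enough "to detect any statistically significant difference for the true kappa of 0.7 and the null kappa of 0.5".

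The Statistical methods section names percentage agreement and weighted kappa and adds no decision rule.

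**The concern.** The error that matters in a non-inferiority trial is accepting the new mode when its true loss equals the margin or exceeds it. A rule that compares an estimate with the margin does not control that error. At a true loss equal to the margin, the estimate falls on the favourable side about half the time, whatever the sample size. Control comes from requiring a confidence bound to clear the margin, or equivalently from rejecting a one-sided null placed at the margin.

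The stated null does not supply this. Significance is a property of a sample result, not of the population, so a null of significant difference cannot be tested as written, and it is not tied to 20%. The Sample size section has the right direction and a margin, but its 5% level is attached to kappa 0.7 against 0.5, not to the between-group difference against 20%.

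This rule produces the trial's answer on whether specialists can rely on video consultation.

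**Working it through.** **Inputs from the article.** 80 per group, 1:1; category rates 25/50/25%; true kappa 0.7, null kappa 0.5; significance level 5% (sidedness not given); power 80%; margin 20% (scale not given).

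**Assumptions.** The abstract's rule applies to the observed difference. Reference agreement is not given. With the stated rates, chance agreement is 0.25² + 0.50² + 0.25² = 0.375, so kappa 0.7 implies agreement of 0.375 + 0.7 × 0.625 = 81.25%. Values from 60% to 90% were also tried.

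**1. The plan's own figure.** For a one-sample test of kappa, n = [(z_α√V0 + z_β√V1)/0.2]². The largest large-sample variances that the 25/50/25 margins allow for unweighted kappa are V0 = 0.5775 and V1 = 0.4017. With a one-sided 5% level:

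n = [(1.645 × 0.760 + 0.842 × 0.634)/0.2]² = 79.5, so 80 (power at 80 is 80.2%).

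The two-sided version gives 102.3. Of the variants tried, only the one-sided, one-sample version gives 80. It tests one group's kappa against a fixed 0.5, so its 5% is not the error rate of the between-group comparison with 20%.

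**2. The abstract's rule on percentage agreement.** Let R and T be the numbers of agreeing pairs among 80 in the Reference and Telemedicine groups, each binomial. The rule passes if (R − T)/80 < 0.20, that is, R − T < 16. For true agreement of 81.25% against 61.25%:

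SE = √(0.8125 × 0.1875/80 + 0.6125 × 0.3875/80) = 0.0698.

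With a half-count correction of 0.5/80 = 0.00625, the pass probability is about Φ(−0.00625/0.0698) = 0.464. Exact enumeration gives 0.463.

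**3. The same with a confidence bound.** Pass if (R − T)/80 + z × SE (estimated) < 0.20, with z = 1.645 (one-sided 5%) or 1.96 (one-sided 2.5%). Exact enumeration:

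| Reference agreement | True loss (points) | Abstract's rule | Bound, 5% | Bound, 2.5% |
|---|---|---|---|---|
| 60% | 20 | 46.6% | 4.6% | 2.3% |
| 70% | 20 | 46.5% | 4.7% | 2.4% |
| 81.25% | 20 | 46.3% | 4.9% | 2.5% |
| 90% | 20 | 46.0% | 5.3% | 2.8% |
| 81.25% | 25 | 21.2% | 0.9% | 0.4% |
| 81.25% | 30 | 6.8% | 0.1% | under 0.1% |
| 81.25% | 0 (power) | 99.9% | 94.4% | 90.1% |
| 70% | 0 (power) | 99.6% | 87.0% | 79.3% |

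Across Reference agreement of 60–90%, the abstract's rule passes 19–23% of trials at a 25-point loss and 5–8% at a 30-point loss.

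**4. The same rule on the kappa scale.** In 100,000 simulated trials with true kappas 0.7 and 0.5, the observed difference is below 0.20 in 49.6% (unweighted), 49.5% (linear weights) and 50.0% (quadratic weights). With 0.7 and 0.4, the figures are 18%, 20% and 24%.

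**5. Power with a bound if the margin is 0.20 kappa.** Both true kappas 0.7, unweighted: SE = √(2 × 0.4017/80) = 0.1002.

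- One-sided 5%: Φ(0.20/0.1002 − 1.645) = 64%.
- One-sided 2.5%: Φ(0.20/0.1002 − 1.96) = 51%.

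The smaller variance 0.388, from a joint table that mixes perfect agreement with independence, gives 65% and 53%. For 80% power, about 120–125 per group (5%) or 153–158 (2.5%) are needed. The two scales are far apart: under the stated rates, 0.20 kappa is 0.20 × 0.625 = 12.5 points of agreement.

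**The case against.** The strongest reply is that the abstract's sentence only reports the margin. It does not say that the difference is the observed one and does not exclude an interval, and a condensed article may leave the interval method to a fuller document. The Sample size section also points to formal testing: it states direction and margin, sets a 5% level, and places the null kappa 0.20 below the assumed true value. The 80 per group reproduces as a one-sided test.

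Part of this stands. The intention is recoverable, and it would be wrong to say that the article has neither direction nor margin. The literal reading of the abstract is an assumption, and the pass rates depend on it. But the point is not only a missing interval method. The article states a criterion and a null hypothesis, neither is a test against the margin, and the one formal calculation concerns a different comparison. An analysis plan that used a confidence bound would be adding to the published criterion and replacing the published null.

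Two stronger readings are tempting and should not be drawn:

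- A reader might infer that a non-significant difference would be taken as non-inferiority. The documents do not say so. The Aims section puts difference in the null, so a claim of similarity would require rejecting it. Pass rates for a rule of that kind are therefore not relevant here.
- A reader might infer that any unacceptable loss passes about half the time. That holds only for a loss equal to the margin; larger losses pass less often.

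**Conclusion.** The concern holds in this form: the stated criterion and the stated null do not control the risk of wrongly declaring video non-inferior at 5%. Read literally, that risk is about 46–47% at a true 20-point loss of agreement with 80 per group, and it hardly changes with Reference agreement between 60% and 90%. On the kappa scale it is about 50% at a loss of 0.20. A confidence-bound rule brings it to 4.6–5.3% or 2.3–2.8%, according to the level chosen. These are error rates at the margin, where a non-inferiority rule is judged, and they rest on applying the abstract's 20% to the observed difference.

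Whether 160 participants suffice for a correct rule depends on the scale of the margin, which the article does not fix. On percentage agreement they give about 80% power or more if Reference agreement is roughly 70% or higher. On a 0.20 unweighted-kappa margin they do not.

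**What to change.** Align the abstract, Aims and objectives, and Sample size on one statement:

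- **Hypotheses.** H0: Reference minus Telemedicine agreement is 20 points or more. H1: it is less than 20 points.
- **Decision.** Declare non-inferiority only if the upper confidence bound of that difference lies below the margin. State the one-sided level, 2.5% or 5%.
- **Scale.** Say whether the 20% means percentage points of agreement or 0.20 kappa units (and with which weights), as the consulted specialists intended it.
- **Power.** Restate it for this test. On percentage agreement with equal true agreement, 160 participants give about 90% (2.5%) or 94% (5%) at Reference agreement of 81%, and 79% or 87% at 70%. On 0.20 unweighted kappa, they give about 51–53% or 64–65%.

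On the percentage scale the cost is a few sentences and essentially no extra participants. On the kappa scale the sponsor must either report the lower power or recruit about 120–125 (5%) or 153–158 (2.5%) per group for 80% power.

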**Discussion:**

Despite rapid growth in application of telemedicine in a variety of medical specialities, little is known about the reliability of videoconferencing for remote consultation of people with diabetes. Results of this proposed study will provide evidence of the reliability of specialist consultation offered by videoconference for people with diabetes.

**Trial registration number:**

Australian New Zealand Clinical Trials Registry ACTRN12612000315819.

## Background

Diabetes Mellitus (DM) is a common disease with increasing prevalence in many countries. More than 366 million people are estimated to have diabetes worldwide and it is projected to increase to 552 million by 2030, affecting 9.9% of the global adult population [1]. Managing diabetes and its complications is very costly, and creates a substantial burden on the health care economy. There is no cure; instead optimal glycaemic control is required to minimize complications [2]. However, less than 70% of people with diabetes are achieving target glycaemic control, demonstrating that effective disease management for people with diabetes remains a challenge [3,4]. For some patients, particularly in rural areas, not achieving target glycaemic controls is at least in part due to poor access to qualified health care providers [5,6]. In response to the growing demand for health care and a decreasing availability of health care providers, information and communications technology (ICT) has shown potential to improve the accessibility of health care services and to reduce costs of health care delivery [7].

Telemedicine is the provision of medical and health services remotely using information and communication technology [8]. The telemedicine interactions are generally divided into two categories: synchronous (occurring in real time such as videoconferencing) and asynchronous (store-and-forward solutions such as transmission of a blood glucose level from a glucometer to a health centre).

Asynchronous (store-and-forward) telemedicine has been successfully implemented in the medical specialities such as pathology [9], radiology [10] and dermatology [11] where real time exchange of information between health care providers and consumers is not essential. In contrast, synchronous telemedicine requires both parties to interact with each other in real time using communication technology. Among the synchronous telemedicine solutions, videoconferencing – real time exchange of voice and image - is becoming popular through rapid achievements in digital communication technology. Video teleconsultation has been used in a wide range of disciplines from emergency medicine [12] to mental health [13], but it has been emphasized that most existing disciple-specific studies cannot be generalized to other tele-medical contexts [14].

In a systematic review on synchronous and asynchronous teleconsultation for diabetes care, Verhoeven et al. suggested that both teleconsultation solutions are feasible, cost-effective and reliable for delivering diabetes care. However they identified a lack of high quality studies and diversity in the included studies [15]. Several studies have reported results of using videoconferencing for diabetes care. However, almost all used videoconferencing for behavioural therapy including diabetes education, self-management training, nutrition counselling, and collaborative goal setting [16]. The accuracy of videoconferencing for specialist telediagnosis and assessment of selected diseases has been studied (e.g., Alzheimer’s disease) [17], but there is no published study on the reliability and accuracy of videoconferencing for clinical consultation with regard to medical specialist evaluation and management of diabetic patients.

If a doctor is able to assess and manage a diabetic patient via videoconference with a similar level of reliability as a face-to-face consultation, the medical profession could have confidence in including video consultation as a regular aspect of their clinical care. A clinician who regularly sees patients for evaluation of their diabetic management may choose to substitute some of the regular face-to-face consultations with a video consultation. This has important implications for patients isolated by either their physical location (e.g., rural communities) or their function (e.g., disabled older people in aged care facilities) and paves the way for at least some specialist consultation for people living in rural or remote areas to avoid the expense and inconvenience of long distance travel. It may also increase the opportunities for some people to receive advice in situations where they previously may have not, due to an inability to travel. This protocol describes a research project that will evaluate the reliability of clinical decisions made during a diabetic patient consultation via videoconference.

Typically the aim of a Randomized Controlled Trial (RCT) is to identify if superiority exists between two or more parallel groups to guide decision making, for example whether to replace a current medication or procedure with a new one. However, an alternative analytical approach is required when the aim is to identify if an innovation is suitable to replace an existing process at the same level of efficacy [18]. Such methodology is referred to as a non-inferiority trial. A priori defined level of clinically acceptable variation between the two modes of delivery is used to determine the outcome. This study is a non-inferiority trial comparing the clinical outcomes of video consultations against those of conventional face-to-face consultations.

### Aims and objectives

In this study we are seeking to identify if telemedicine is a reliable vehicle for providing specialty consultation for people with diabetes using videoconferencing, with the implication that it would be useful to utilise when usual care is either not available or difficult to deliver. The aim of the study is to test the level of clinical agreement achieved using specialist to patient videoconferencing (VC) compared with face-to-face (FTF) consultation. To place this level of agreement in context, it will also establish the level of agreement among specialists using face-to-face consultation. This approach enables the variation in clinical decision making among clinicians to be identified, and thus to be differentiated from the effect of the VC mode of service delivery.

This study will test the hypothesis that the clinical assessment and recommendations as determined by an alteration in medication type or dose made by endocrinologists for people with diabetes via videoconference are significantly different from those made through face-to-face consultation (null hypothesis). Secondary hypotheses will apply the same analytic techniques to the other aspects of diabetes consultation: (i) ordering lab tests or other diagnostic intervention; (ii) initiation of new medication(s) or dose adjustment of the previously prescribed drugs for dyslipidaemia and/or hypertension; (iii) detection or management of diabetes related complications; and (iv) referring to other specialists or arranging hospital admission.

## Methods/design

This study is a repeated-measure non-inferiority randomized controlled trial. All patients participating in the study will receive two consultations (one original consultation and one additional consultation; called paired-consultation in this paper) by two different endocrinologists. Level of agreement between the recommendations made via VC versus FTF for the same patient by two endocrinologists will be calculated. This constitutes VC-FTF paired-consultations. Since there is likely to be a certain level of clinical variability between clinicians, the level of agreement in VC-FTF paired-consultations will then be compared against the level of agreement between two endocrinologists when they consult a patient in standard clinical practice (FTF-FTF). This arrangement will determine whether any lack of agreement is likely to be a result of the videoconference modality, or just normal variation between doctors.

### Study setting and participants

This study will be conducted in the outpatient diabetes clinic of the Princess Alexandra Hospital (PAH) which is a tertiary teaching hospital in Brisbane, Australia. People with diabetes who have an appointment with an endocrinologist as a new or review case for the purpose of improving management of their diabetic condition will be approached and invited for participation. Six endocrinologists who attend the clinic routinely will visit the patients as scheduled (these are referred to as ‘routine endocrinologists’ in this paper). Another endocrinologist (referred to as the ‘research endocrinologist’ in this paper) will be employed for the purpose of this research to undertake the additional consultation for each patient who consents to participate in the trial. The additional consultation will be conducted by the research endocrinologist prior to the original consultation for each patient. However, the participant patients will receive both their consultations on the same day in the same clinic session. The routine and research endocrinologists are all specialist doctors with the same qualifications and credentials (i.e. accredited by the Royal Australian College of Physicians).

### Inclusion and exclusion criteria

Eligible participants include patients (i) with a confirmed diagnosis of diabetes, (ii) who are 18 years of age or older. Patients will be excluded if (i) they are severely ill, (ii) unable to communicate effectively (blind, deaf, mute, etc.), or (iii) speak in a language other than English if an interpreter is not available.

### Randomisation

Participants will be randomly allocated in a 1:1 ratio into one of two study groups (Telemedicine or Reference group). In the Telemedicine group the participants will receive a paired-consultation in which one of the consultations is via video (FTF-VC or VC-FTF), but in the Reference group both consultations will be face-to-face (FTF-FTF). Figure 1 outlines the randomisation and allocation process. The first consultation in each paired-consultation will be provided by the research endocrinologist, whereas the second consultation will be provided by one of the routine endocrinologists of the clinic. Since the order of VC vs. FTF consultations are also randomised, there will be three potential configurations for the paired consultations of each participant (Table 1). With such design, half of the video consultations will be conducted by the research endocrinologist, and the other half by the routine endocrinologists of the clinic.

